## Abstract

RiSE study aims to evaluate a race-based stress-reduction intervention as an effective strategy to improve coping and decrease stress-related symptoms, inflammatory burden, and modify DNA methylation of stress response-related genes in older AA women. This article will describe genomic analytic methods to be utilized in this longitudinal, randomized clinical trial of older adult AA women in Chicago and NYC that examines the effect of the RiSE intervention on DNAm pre- and post-intervention, and its overall influence on inflammatory burden. Salivary DNAm will be measured at baseline and 6 months following the intervention, using the Oragene-DNA kit. Measures of perceived stress, depressive symptoms, fatigue, sleep, inflammatory burden, and coping strategies will be assessed at 4 time points including at baseline, 4 weeks, 8 weeks, and 6 months. Genomic data analysis will include the use of pre-processed and quality-controlled methylation data expressed as beta (***β***) values. Association analyses will be performed to detect differentially methylated sites on the targeted candidate genes between the intervention and non-intervention groups using the Δ***β*** (changes in methylation) with adjustment for age, health behaviors, early life adversity, hybridization batch, and top principal components of the probes as covariates. To account for multiple testing, we will use FDR adjustment with a corrected p-value of <0.05 regarded as statistically significant. To assess the relationship between inflammatory burden and Δ***β*** among the study samples, we will repeat association analyses with the inclusion of individual inflammation protein measures. ANCOVA will be used because it is more statistically powerful to detect differences.

## Introduction

### Impact of psychosocial stress on DNAm

Changes in DNA methylation (DNAm) may be some of the earliest cellular events in disease onset [1], such aberrant changes have been linked to inflammatory burden [2, 3] and a broad range of diseases including cardiometabolic disease (CMD) [4, 5]. Compelling evidence demonstrates that DNAm is associated with early life adversity [6–8], social stress [9], and history of trauma [10, 11]. Our recent epigenome-wide association study [12] revealed that greater levels of perceived discrimination are associated with decreased DNAm at seven CpG sites linked to inflammatory disease-associated genes in a sample of African American (AA) women [12]. Importantly, DNAm associated with psychological stress is malleable [13], making it a prime target for psychobehavioral interventions [13–16]. To date, only a few studies have explored the impact of psychobehavioral interventions on changes in DNAm of stress response-related genes with the majority focusing on mindfulness interventions. In a small study of veterans with post-traumatic stress disorder who participated in a mindfulness-based stress reduction program, investigators found that, in addition to improvements in trauma symptoms, participants also had an increase in methylation of the FKBP5, a gene involved in modulating glucocorticoid receptor activity [17, 18]. Others have found a decrease in methylation of SLC6A4, a gene related to serotonin transport, following participation in a three-month mindfulness program [19]. In a small randomized, wait-listed control trial, women who participated in an 8-week yoga intervention had reduced methylation of the TNF region as compared to women in the control group [20]. Changes in DNAm have also been associated with tai chi [21], psychotherapy [22], and meditation [23]. The most commonly identified genes associated with DNAm changes following a psychobehavioral intervention include SLC6A4 [19], FKBP5 [22, 24], and BDNF [25, 26].

### Importance of genomics

Genomics has brought significant contributions to cardiovascular disease (CVD) research [27], particularly among AAs, including the combined effects of genetics and cigarette smoking on systolic BP [27] and the effects of body mass index (BMI) on DNAm [28]. DNAm is one type of epigenetic process that modulates gene expression by adding or removing methyl groups to DNA in response to the environment. Studies demonstrate that hyper or hypo methylation of genes due to chronic stressors, including racism and discrimination, are significantly associated with CMD risk [29–36]. Emerging evidence demonstrates that psychobehavioral interventions may modify the methylation of stress response-related genes (e.g., TNF, SLC6A4, FKBP5) [15, 21], potentially buffering the impact of psychological stress at the molecular level. However, few studies have examined the impact of a psychobehavioral intervention on changes in DNAm and none have addressed chronic stress in older AA women.

Here we will describe the methods that will be utilized in a randomized clinical trial of AA Women in Chicago and New York City that examines the effect of the RiSE intervention on DNAm pre and post-intervention, and its overall influence on cardiometabolic risk outcomes over time. We will use a targeted candidate gene approach by selecting 20 stress-related candidate genes (and their corresponding CpG sites), assessing DNAm pre and post-RiSE and their association with the outcome measures of cardiometabolic risk (perceived stress, depressive symptoms, and fatigue and sleep disturbance). **See Table 1 and Fig 1.**

**Fig 1 pone.0295293.g001:**
[figure not shown]
Study period. Schedule of enrollment, interventions, and assessments.

**Table 1 pone.0295293.t001:** Sample size estimation based on preliminary date. *Assumes n = 125 per group complete cases and *α* = 0.05; r-squared of 5 covariates is 0.30, **The smallest mean difference necessary to ensure > 80% power, assuming pooled SD observed in the pilot.

Outcome evaluated at 6 months	RiSE Mean	Control Mean	|Δ| Means	Pooled SD	Effect size	Power*	Mean difference for 80% power**
	Observed: Pilot Data @ 8 weeks						
WCQ-Active coping	23.76	24.77	1.01	8.24	0.06	21%	2.45
WCQ-Avoidance coping	8.14	14.38	6.24	5.25	0.59	>99%	1.56
WCQ-minimize situation	11.21	14.04	2.83	4.36	0.32	>99%	1.30
DASS-21: Depression	1.45	3.13	1.68	3.09	0.27	>99%	0.92
DASS-21: Anxiety	2.39	3.31	0.92	3.41	0.13	72%	1.02
DASS-21: Stress	4.45	5.90	1.45	4.05	0.18	92%	1.20
TNF-a	0.95	1.00	0.05	0.36	0.07	26%	0.11
High-sensitivity C-reactive protein (hsCRP)	3.83	7.24	3.41	6.30	0.27	>99%	1.88

*Resilience*, *Stress*, *and Ethnicity* (RiSE) [37–39], is a group-based, 8-week intervention that integrates cognitive-behavioral strategies [40] focused on the biopsychosocial impact of racism [41, 42], racial identity development [43–45], and empowerment [46]. The conceptual model for the study is based on allostatic load theory [47] which posits that accumulating stress or “wear and tear” results in negative physiological consequences. **See Fig 2.**

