### Procedures

Detailed descriptions of this study have been previously discussed [90]. Briefly, this convenience sample will include 300 self-identified AA women residing in either the Chicagoland (n = 150) or New York City (n = 150) area between the ages of 50 and 75 years with risk factors for CMD [91]. Participants will be randomized to either an 8-week RiSE intervention or a Health Education Program (HEP) (attention control). Potential participants will be pre-screened for eligibility over the phone and will be followed by an appointment for further screening if the potential participant is eligible. After collecting informed consent for obtaining inflammatory markers and DNAm samples, the samples will be stored in a lab for processing and frozen for later batch analysis. DNAm samples will be stored at 4°C. Specimens will be shipped overnight on dry ice to respective labs for analysis per best practice guidelines [92]. Individuals will contribute data for up to four-time points (baseline, 4 weeks (mid-intervention), 8 weeks (completion of intervention), and 6 months post-intervention). Data will be collected from participants using an Audio Computer-Assisted Self-Interview system (ACASI) [93]. Perceived stress, depression, fatigue, and sleep disturbance symptoms will be analyzed via the Perceived Stress Scale (PSS-10) [94], Patient Health Questionnaire 9 (PHQ 9) [95], NIH PROMIS Fatigue Short Form 8a [96], and NIH PROMIS Short Form v1.0 [97].

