#### Genomic data analysis

Using the pre-processed and quality-controlled methylation data expressed as beta values which are the percentage methylation at each CpG site at specific targeted candidate genes, we will determine changes in methylation (Δ***β***) at every site as the difference between methylation at baseline and methylation at post-intervention. Negative Δ***β*** indicates a decrease in methylation from baseline to post-intervention, and a positive value indicates an increase in methylation from baseline to post-intervention. Association analyses will be performed to detect differentially methylated sites on the targeted candidate genes between the intervention and non-intervention groups using the Δ***β*** with adjustment for age, health behaviors, early life adversity, hybridization batch, and top principal components of the probes as covariates. To adjust for multiple testing, we will use False Discovery Rate (FDR) adjustment with an FDR of <0.05 regarded as statistically significant. All analyses will be performed in R software using the Bioconductor R package ‘limma’ [115]. To assess the relationship between inflammatory burden (IL-6, TNF-α, IL-1β, IFN-γ, CRP) and Δ***β*** among the study samples, we will repeat the above association analyses with the inclusion of individual inflammatory protein measure.

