## Discussion

### Potential pitfalls, alternative approaches

Given the longitudinal nature of this study and the significant commitment necessary to participate in the study, attrition is an inherent potential issue. In our preliminary work, we found an 11% attrition rate with a similar design. For this study, we will conservatively over-sample by 20% to accommodate potential attrition to achieve n = 250 participants with complete data at 6 months. We will minimize attrition by collecting multiple phone and email/text messaging contact information for participants and reviewing this information at each visit. It is possible that some participants may not have access to the internet or have technical challenges with Zoom. We will provide iPads and internet access for participants who lack equipment and/or internet access. In addition, our study team will teach participants how to use Zoom as needed and be available in real time to address technical issues. To note, synchronous online platforms have successfully been used to administer group-based psychobehavioral interventions, including in older populations [116–119]. Further, we have experience successfully conducting research groups via Zoom ([name]: PCORI). Despite these limitations, the proposed study will be designed and implemented with the highest degree of scientific rigor and has the potential for significant public health impact. Finally, by providing concrete recommendations based on the results of this intervention, we believe that this is the first study to provide the needed science to implement interventions focused on reducing the impact of multiple forms of stressors on the CMD health of AA women by exploring the biological changes in DNAm and inflammation that may contribute to this disparity.

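### RiSE is delivered in groups, but the Table 1 power figures and the listed limma model make no allowance for correlation within intervention groups

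*Protocol article*

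**What the plan says.** The Introduction, just after Table 1, describes RiSE as a programme that "is a group-based, 8-week intervention that integrates cognitive-behavioral strategies". The Discussion (Potential pitfalls, alternative approaches) returns to group delivery when it defends online sessions: "synchronous online platforms have successfully been used to administer group-based psychobehavioral interventions".

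Allocation is of participants, under Procedures: "Participants will be randomized to either an 8-week RiSE intervention or a Health Education Program (HEP) (attention control"). The article does not say whether HEP also meets in groups, how large the RiSE groups are, or how many there will be.

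Table 1 bases its power on few assumptions: "Assumes n = 125 per group complete cases", alpha 0.05, and "r-squared of 5 covariates is 0.30". Its last column is defined as "The smallest mean difference necessary to ensure > 80% power, assuming pooled SD observed in the pilot". The only inflation of the sample anywhere in the article is 20% for attrition.

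The limma analysis of methylation change (Genomic data analysis) is to be done "with adjustment for age, health behaviors, early life adversity, hybridization batch, and top principal components of the probes as covariates". ANCOVA is named in the Data analytic plan without its model terms or variance structure.

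**The concern.** When individuals are randomised and then treated together for 8 weeks, members of one group can end up more alike than members of different groups. The variance of the treatment comparison then contains a between-group component. An analysis that treats participants as independent leaves it out, so confidence intervals are too narrow and p-values too small. A power calculation on the same footing promises more than the trial can deliver.

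Two things that the article states are exposed to this: the power figures and detectable differences in Table 1, and the limma model, whose covariates include hybridization batch but not intervention group. The same mechanism could raise the number of false discoveries among the roughly 4000 CpG tests.

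**Working it through.** **Inputs from the article.** From Table 1: 125 complete cases per arm, alpha 0.05 (sidedness not given; two-sided reproduces the table), covariate R² 0.30, and the pilot differences and SDs. Two rows serve as examples. DASS-21 Stress has difference 1.45, SD 4.05, power 92% and 80%-power difference 1.20. The Anxiety row reads "DASS-21: Anxiety 2.39 3.31 0.92 3.41 0.13 72% 1.02".

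**Step 1: reproduce Table 1 under independence.**
SE = SD × √(1 − 0.30) × √(2/125); power ≈ Φ(difference/SE − 1.96).
- Stress: SE = 4.05 × 0.8367 × 0.1265 = 0.429; 1.45/0.429 = 3.38; power 92% (stated 92%).
- Anxiety: SE = 3.41 × 0.8367 × 0.1265 = 0.361; 0.92/0.361 = 2.55; power 72% (stated 72%).
- Active coping gives 21% and TNF-a 26%, both as stated. The other four rows exceed 99%, as stated.
- The tabulated 80%-power differences give 80% to 82% power. The 82% is TNF-a, where 0.11 is rounded.

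All eight rows match with a design effect of 1. A design effect of only 1.09 would already give 90% for Stress and about 69% for Anxiety, so the published figures contain no allowance.

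**Step 2: assumptions the article does not supply.** Group size m = 10 and ICC 0.01, 0.05 or 0.10, with the ICC taken on the covariate-adjusted residual. These values are for illustration only.

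**Step 3: variance factor.**
- Both arms in groups: DE = 1 + (m − 1) × ICC.
- Only RiSE in groups: the mean of that and 1, so DE = 1 + (m − 1) × ICC/2.

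**Step 4: consequences.** True Type I error of an unadjusted nominal 5% test = 2 × [1 − Φ(1.96/√DE)]. Power with the variance correctly stated = Φ(difference/(SE × √DE) − 1.96).

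| ICC (m = 10) | Arms clustered | DE | Type I error | Stress power | Anxiety power |
|---|---|---|---|---|---|
| 0 | – | 1.00 | 5.0% | 92% | 72% |
| 0.01 | both | 1.09 | 6.0% | 90% | 69% |
| 0.01 | RiSE only | 1.045 | 5.5% | 91% | 70% |
| 0.05 | both | 1.45 | 10.4% | 80% | 56% |
| 0.05 | RiSE only | 1.225 | 7.7% | 86% | 63% |
| 0.10 | both | 1.90 | 15.5% | 69% | 46% |
| 0.10 | RiSE only | 1.45 | 10.4% | 80% | 56% |

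At ICC 0.05, the 80%-power differences in Table 1 deliver about 64–67% (both arms) or 71–74% (RiSE only). To restore 80%, the Stress difference of 1.20 would have to grow to 1.20 × √1.45 = 1.44, or to 1.20 × √1.225 = 1.33.

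**Step 5: wider range.** For m from 6 to 15 and ICC from 0.01 to 0.10, Type I error runs from 5.6% to 20.6% (both arms) or 5.3% to 13.3% (RiSE only). A nominal 80% power becomes 78% to 44%, or 79% to 57%. Depression and hsCRP, stated as >99%, stay at 91% or more throughout.

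**Step 6: degrees of freedom.** With 250/10 = 25 groups, a group-level test in both arms has 23 df. That lowers power a little further: Stress at ICC 0.05 goes from 80% to 77%. Part of this loss is not due to correlation, since at ICC 0 the df change alone takes Stress from 92% to 90%.

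**The case against.** The case against has several parts, and some of them stand.

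- **Unspecified models.** A reader might infer that the ANCOVA ignores clustering. The article gives no ANCOVA model and refers to a fuller description of the study published elsewhere, so its variance structure may be set there or in the SAP. The inference is not supported.
- **All power figures.** A reader might extend the Table 1 result to the pwrEWAS calculation under Power analysis. Its inputs and plot are not available, so it cannot be recomputed. One can say only that no allowance is stated.
- **Certainty of harm.** Standard errors are too small only if the ICC is above zero, and the article gives neither ICC nor group size. This stands. But a zero ICC is not argued for either, and it is an optimistic default for an intervention delivered in groups.
- **FDR.** A reader might conclude that the stated FDR of 0.05 will not be achieved. That would need an assumed ICC applied across about 4000 CpGs. Nothing in the article shows that 6-month change in salivary methylation clusters by session group, and cell type, batch and plate effects are already addressed. The direction of the risk is clear; its size is not known.
- **One arm or two.** HEP is called an attention control without mention of groups. If only RiSE is clustered, the effect is smaller, as the table shows.
- **Choice of example.** DASS-21 is the pilot measure. For stress and depressive symptoms, Procedures names PSS-10 and PHQ-9. The rows show how sensitive the published figures are, and no more.

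A later analysis plan could add a group term. It would not change the fact that Table 1 as published rests on independence.

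**Conclusion.** The point holds in a limited form. Group delivery is stated, Table 1 contains no design effect, and the listed limma model has no term or block for intervention group. If outcomes correlate within groups, precision and power are overstated. The size depends wholly on assumed values. With 10 per group and ICC 0.01/0.05/0.10, a nominal 5% test has a true error rate of about 6.0%/10.4%/15.5% with both arms clustered, or 5.5%/7.7%/10.4% with RiSE alone. The loss of power matters for the Stress and Anxiety rows and for the 80%-power column. The rows above 99% hardly move. For the pwrEWAS power and the ANCOVA the finding is only that no allowance is stated, and for the CpG tests the effect on false discoveries cannot be put into figures.

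**What to change.** - Record an intervention-group identifier for every participant in each arm delivered in groups, and state whether HEP is one of them.
- In limma, account for the group through duplicateCorrelation with the intervention group as block, or fit a mixed model for each CpG.
- In the ANCOVA, add a random effect for intervention group with small-sample degrees of freedom. If HEP is not run in groups, use a partially nested model with the group effect in the RiSE arm only.
- Restate Table 1 with a design effect over a stated group size and ICC range. The last column is multiplied by √(1 + (m − 1) × ICC) if both arms are in groups, or by √(1 + (m − 1) × ICC/2) if only RiSE is. State whether the pwrEWAS figure includes any such allowance.

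The cost is one extra variable, best recorded while groups are running, and a modest change to the models. Confidence intervals will widen and stated power will fall. No extra participants are required.

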**Fig 2 pone.0295293.g002:**
[figure not shown]
Conceptual model.

Based on our preliminary work, we anticipate that participation in RiSE will reduce psychological distress and inflammation. RiSE is a stress reduction intervention that has been shown to be effective in improving coping among AA women [48]. Further, in a targeted candidate gene analysis and epigenomic study in AA women, we found that DNAm patterns of four genes related to the regulation of blood pressure (BP) were associated with stress overload, problem-solving coping, social support coping, and avoidance coping [49], although these associations were not significant after correcting for multiple testing. Others have reported associations between DNAm and stress-related symptoms such as perceived stress, depressive symptoms, fatigue, and sleep [50–52].

Psychosocial stressors, such as discrimination, racism, and social context (e.g., socioeconomic status), when chronic and relentless, can impact the DNAm of stress-response related genes [12, 53], altering the expression of genes that regulate inflammatory response to stress [53]. Based on our preliminary data as well as evidence from other stress reduction interventions [54, 55], we propose that RiSE will improve stress-related symptoms and decrease inflammation (e.g., CRP, IL-6 TNFα, IL-1β, and IFN-γ) [38].

We will use a targeted candidate gene approach by selecting 20 genes (and their corresponding CpG sites) that are associated with our outcome measures to assess DNAm modifications following RiSE (**Table 2**).

**Table 2 pone.0295293.t002:** Stress-related candidate genes and functions.

Gene	Function	Gene	Function
FKBP5	Encodes FK506-binding protein 51. Pleiotropic effects on stress and inflammation, associated with CMD [56]	PAC1	Regulates PACAP which is linked to the stress response [57]
SLC6A4	Codes for the serotonin transporter and is associated with depression [58]	5-HTT	Regulation of serotonin transporter protein which is associated with depression and stress [59]
BDNF	Regulates neurogenesis in brain. Alterations of BDNF associated with stress and plays role in regulating body weight [60, 61]	CRF	Regulates homeostasis and neuroendocrine response to stress [62]
TNF	Encodes proinflammatory cytokine. Associated with atherosclerosis [4, 63]	TLR1	Mediates cytokine secretion and inflammatory response to stress [62]
OXTR	Encodes oxytocin receptor and is associated with range of psychological responses [64]	COMT	Instructs enzyme that regulates neurotransmitters associated with stress [65]
IL-6	Regulates proinflammatory cytokine IL-6 [66]	OPRM1	Provides instructions for making mu opioid receptor which is associated with PTSD [67]
NR3C1	Encodes glucocorticoid receptor associated with stress response and CMD [68–70]	KITLG	Inhibitory role on natural killer cells. Associated with cortisol stress reactivity [71]
AVP	Encodes member of vasopressin/oxytocin family. Plays role in glucocorticoid signaling [62]	DNMT-1	Provides instructions for making DNA methyltransferase 1 which is associated with stress response as well as CMD [4, 72, 73]
GABA	Provide instructions for making GABAA receptor protein which produces calming effect [74]	HSD11β2	Implicated in glucocorticoid regulation and response to stress. Associated with CVD [75, 76]
MAOA	Regulates monoamine oxidase A that is related to psychosocial stress [77]	ACE	Regulates angiotensin converting enzyme which is associated with depression and CVD [78]

Our candidate genes were selected based on those consistently associated with stress response in the literature (see **Table 2**). Several studies have demonstrated that DNAm can be modified within weeks to months following changes in environmental factors [79–81]. In those previous studies of longitudinal change of DNAm, a large variation of inter-individual differences over time has been observed [82]. Therefore, our proposed 6-month follow-up not only provides a reasonable time frame to investigate the longitudinal change in DNAm but also links to socio-behavioral stressors among AA women, which have not been previously studied.

